**Figure 1 figure1:**
[figure not shown]
Study timeline.

**Table 1 table1:** Example strategies for implementing the teaching personal and social responsibility (TPSR) framework in physical education (PE) settings.

Levels	Explanation	Social outcomes in New South Wales PDHPE^a^ K-10 syllabus	Examples in PE setting
Respect for the rights and feelings of others	Demonstrating empathy for and understanding of other students’ feelings	Interact respectfully with others (“Rationale,” page 10) Stage 4: PD4-2^b^; PD4-3^c^; PD4-10^d^	Social “theme” of each lesson (eg, cooperation, teamwork, and leadership) Eye contact Not raising one’s voice during a confrontation
Effort and teamwork	Providing all students, regardless of skill level, the opportunity to be involved and included	Develop social skills (“Rationale,” page 10) Outcome: PD4-3; PD4-10	Team huddles Strategy time Giving everyone a turn
Self-direction and goal setting	Students’ role in the activity, their goals, and the goals of the team; collaboration between the two domains	Develop self-management skills with self-confident, socially responsible citizens (“Rationale,” page 10) Outcomes: PD4-2; PD4-9^e^	Discussing strategy Problem-solving Giving and embracing roles during games Students proposing modifications to the games
Helping and leadership	Demonstrating and developing leadership opportunities through play	Development of interpersonal skills (“Rationale,” page 10) Commitment to lead and promote healthy, safe, and active lives (“Values and attitudes,” page 13) Outcomes: PD4-2; PD4-3; PD4-10	Equipment roster Coaching and refereeing responsibilities Students acquire special roles independent of the teacher Student-teacher is chosen to instruct the group on the activities for the day instead of the teacher A new captain is chosen for each lesson
Transfer	How TPSR and the skills learned in lessons can be applied to other facets of life	Advocate for health, safety, and well-being of themselves and others in the community and beyond school (“Rationale,” page 10) Outcome: PD4-10	Reflective class discussion on how learning in this setting can be applied to other settings Student discussions in pairs

^a^PDHPE: personal development, health, and physical education.

^b^PD4-2: a student examines and demonstrates the role help-seeking strategies and behaviors play in supporting themselves and others.

^c^PD4-3: a student investigates effective strategies to promote inclusivity, equality, and respectful relationships.

^d^PD4-10: a student applies and refines interpersonal skills to assist themselves and others to interact respectfully and promote inclusion in a variety of groups or contexts.

^e^PD4-9: a student demonstrates self-management skills to effectively manage complex situations.

**Table 2 table2:** Intervention timeline.

Terms and weeks		Tasks
**Term 2**		
	8	Preintervention testing PSRQ^a^ and PACES-PE^b^ surveys administered
	9	Back-up dates for surveys
	10	—^c^
**Term 3**		
	1 (athletics)	Zoom check-in (occurs every week) “Every name, every day” Class Goal HERO concept “Me time” “Good Game” at the conclusion of the lesson “Coaches and Players” in 3-week intervals
	2 (athletics)	TARE^d^ analysis
	3 (athletics)	—
	4 (athletics)	—
	5 (athletics)	TARE analysis
	6	—
	7	—
	8	TARE analysis
	9	—
	10	Postintervention testing PSRQ and PACES-PE surveys administered Focus groups completed
**Term 4**		
	Week 5	Follow-up

^a^PSRQ: Personal and Social Responsibility Questionnaire.

^b^PACES-PE: Physical Activity Enjoyment Scale–Physical Education version.

^c^Not applicable.

^d^TARE: Tool for Assessing Responsibility-Based Education.

### Outcomes

The primary outcomes addressed within the intervention are personal responsibility, social responsibility, and leadership, reflecting the levels of the TPSR framework. The secondary outcomes include enjoyment, feasibility, and acceptability. To obtain a comprehensive analysis of the TPSR framework within a school system, the proposed outcomes will provide valuable insights into how the framework influences student behavior and overall intervention effectiveness.

Baseline characteristics will include age, gender, boarding status (boarding vs nonboarding), school type, and SES (via postcode).

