### Participants

The participants in this study will be students from years 5, 6, and 8. Each intervention group in the study will need to have 77 students and a matched control group of the same size to detect 2-tailed statistical significance (*P*<.05) with 80% power (1−β=0.8). Two schools in the western suburbs of Sydney have been recruited to participate in the study: one is a government high school, and the other is an independent K-12 school. They have been chosen through professional networks who expressed interest in the TPSR study. Students in NSW generally participate in 1 PE lesson per week, which is where the intervention will take place. PE lessons in NSW high schools are delivered to students from years 7 to 10 and focus on skills development, alongside one or two sport lessons focused on game play.

Consent will be obtained from parents, students, and the school principals in line with the ethics requirements of the University of Sydney. Participants’ personal information and school names will be deidentified in all publications arising from the study. Students and teachers will also be briefed on the intervention before study commencement and given the opportunity to ask questions. Participants will be allowed to withdraw from the intervention at any time. All data collected, including data from focus interviews, surveys, meeting minutes, and consent forms, will be stored securely and encrypted with a password. If parents request details of intervention results, a lay summary will be provided.

Fidelity and acceptability will be addressed through teacher expertise and training, intervention location, timetabling, and time spent on the intervention. Teachers will participate in a professional development program before starting the intervention. The purpose of this program is to familiarize teachers with the TPSR framework and to facilitate the co-design of strategies and activities to integrate the framework into programs. This approach also means that students do not have to build relationships with or adapt to outside facilitators. Furthermore, it does not incur additional funding for the school or research team. The professional development program will comprise a 3-hour, face-to-face learning block before the intervention and ongoing check-ins with teachers using Zoom (Zoom Video Communications, Inc) for the duration of the intervention.

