### Measurement Tools

The Personal and Social Responsibility Questionnaire (PSRQ) will be used to measure the primary outcomes of the study: personal responsibility, social responsibility, and leadership. This questionnaire has been used in previous TPSR studies and has been deemed valid and reliable [30,31]. It consists of 14 items split into 2 categories (personal responsibility and social responsibility) [30]. Participants will complete the PSRQ in the pretest and posttest phases of the intervention and will be assured that there are no right or wrong responses and that their responses will remain anonymous. The TARE is an observational tool aligned with the TPSR model. The second part focuses on whether teachers have included elements such as modelling respect and setting expectations within their lessons [32]. The secondary outcomes of the study will be enjoyment, feasibility, and acceptability. These outcomes will be measured using the Physical Activity Enjoyment Scale–Physical Education version (PACES-PE), which is an 11-item measurement tool designed to measure enjoyment levels in adolescent children using a Likert scale and revised, student-friendly questions [33]. The PACES-PE has been used in PE-based studies previously and demonstrated positive results in female adolescent populations, particularly through the link between enjoyment and increased rates of physical activity [33].

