#### Quantitative Analysis

Quantitative data from the PSRQ, PACES-PE, and TPSR will be analyzed using SPSS software (version 30.0; IBM Corp). Internal consistency of the scales will be assessed using Cronbach α. The PSRQ will assess students’ self-perceived levels of personal and social responsibility, and the PACES-PE will assess enjoyment in PE. ANOVA will be conducted to compare mean scores before and after the intervention for both questionnaires. TARE data will be collected through lesson observations by the research team 3 times during the 10-week intervention period, and interrater reliability will be assessed using Cohen κ. Frequencies and mean scores of the TPSR strategies will be examined descriptively and across time to explore implementation fidelity. A repeated measures multivariate ANOVA will be performed to provide a more complex analysis of the findings and a more comprehensive view of how the intervention affects multiple variables simultaneously.

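### Three unranked primary outcomes, of which only two are scored, share one sample size at unadjusted two-tailed P<.05; the primary tests and the power statement need a stated multiplicity rule

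*Protocol article*

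**What the plan says.** - **Outcomes section:** "The primary outcomes addressed within the intervention are personal responsibility, social responsibility, and leadership". No outcome is placed first.
- **Measurement Tools section:** the PSRQ is said to measure all three. Of the instrument itself, the section says: "It consists of 14 items split into 2 categories (personal responsibility and social responsibility"). No leadership score is described. The Intervention Design section then restates the main focus as personal and social responsibility only, referring to the measurement tool.
- **Participants section:** "Each intervention group in the study will need to have 77 students and a matched control group of the same size", at two-tailed P<.05 and 80% power. No outcome, effect size, standard deviation or number of tests is attached to the figure.
- **Quantitative Analysis section:** "ANOVA will be conducted to compare mean scores before and after the intervention for both questionnaires". Later in the same section: "A repeated measures multivariate ANOVA will be performed to provide a more complex analysis of the findings". Nothing says that the single-outcome tests depend on the multivariate result. TARE observations, which the abstract lists as a tool for the primary outcomes, are used here descriptively, for implementation fidelity.

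**The concern.** The set of primary outcomes and the sample size belong to the protocol, and both are stated here. Read together, they do not say how many primary tests there are or which result would show an effect. The count is three in one section and two in another. Each test appears to run at the full .05, and the multivariate ANOVA is described as an additional analysis. A reader following the text could present any one of several P<.05 results as primary evidence of impact. The Study Design section justifies the quantitative component by past criticism that this framework lacks quantitative evidence, so an inflated false-positive rate would weaken what the study sets out to supply. The 80% power claim has the same difficulty: without a success rule, it is unclear what it is the power to show.

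**Working it through.** **Inputs from the protocol article.** 77 per group, 1:1, two-sided alpha .05, power 80% (Participants). Three declared primaries (Outcomes). Two PSRQ categories (Measurement Tools).

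**Assumptions.** The article gives no effect size and no correlation between outcomes. The effect is back-solved from 77, and correlations from 0 to 0.9 are shown. Students are treated as independent, so clustering by class is ignored throughout.

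**1. The plan's own figure.** The figure of 77 cannot be reproduced from stated inputs. Solving for the standardised effect in a two-sample comparison:

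d = (z₀.₉₇₅ + z₀.₈₀) × √(2/77) = (1.960 + 0.842) × 0.1612 = 0.4515

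The t-test version gives 0.454. Going the other way, d=0.45 needs 78 per group by the normal formula. So 77 is compatible with a single unadjusted two-sided test at d of about 0.45. It does not prove that this was the derivation.

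**2. Familywise error with each test at two-sided .05.** For independent tests it is 1 − 0.95^m: 1 − 0.95² = 9.75% and 1 − 0.95³ = 14.3%. For correlated tests it was simulated with 1,000,000 equicorrelated normal draws.

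| Correlation | Two PSRQ scores | Three tests |
|---|---|---|
| 0 | 9.75% | 14.3% |
| 0.3 | 9.5% | 13.6% |
| 0.5 | 9.1% | 12.5% |
| 0.7 | 8.3% | 11.0% |
| 0.9 | 7.0% | 8.4% |

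**3. Power with two primaries under Holm, 77 per group, d=0.454.** The first step uses alpha .05/2 = .025.

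- Power for a given outcome at the first step (noncentral t): 71.0%. This is also approximately its power under Holm when the other outcome has no effect.
- Effect detectable with 80% power at the first step: (2.241 + 0.842) × √(2/77) = 0.497; the t-test version gives 0.501, so about 0.50.
- Size needed to keep 80% at the first step for d=0.454: 94 per group.

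With both effects real and equal (simulation, normal approximation):

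| Correlation | Per outcome, full Holm | At least one | Both |
|---|---|---|---|
| 0 | 77.5% | 92% | 63% |
| 0.5 | 76.4% | 85% | 68% |
| 0.7 | 75.9% | 82% | 70% |
| 0.9 | 75.1% | 77% | 73% |

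**4. Larger enrolment.** The abstract expects about 90 students per school at two schools, and Study Design splits each school's classes roughly equally. That implies about 90 per arm. At 90 and d=0.454, first-step power is 78%, and full Holm gives about 83–84% per outcome for correlations from 0.7 down to 0.

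**The case against.** The strongest reply is that ranking outcomes, choosing a correction and defining a positive trial are commonly left to the analysis plan, which is not shown, and that a condensed article need not repeat them. That stands as far as it goes: the absence of a named correction is not, by itself, an error. What the article does state is a three-outcome primary set that conflicts with its own instrument and with a later section, next to a single power claim attached to none of them.

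A reader might infer more than the documents support, in three ways.

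- **That the false-positive rate is 11–14%.** This needs three confirmatory tests and correlations no higher than 0.7. No leadership score or test is described, so the figure for the two scored outcomes is about 7–10%.
- **That 77 per group delivers 80% power only if every outcome is tested uncorrected.** This is not so. A fixed sequence tests its first outcome at the full .05 and keeps 80% for it. A Holm rule requiring at least one of two gives 82–92% at correlations from 0.7 down to 0 if both effects are real. A multivariate test used as a single global gate is another possibility.
- **That the sample size was derived for a single test.** The article does not say so. The fit at d of about 0.45 comes from back-solving under that same model, so it is not independent confirmation. The model also leaves out the planned repeated-measures structure.

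The choice of Holm over a hierarchy is partly judgement. Changing a declared primary outcome in a registered trial is also more than rewording.

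**Conclusion.** The point holds in a limited form. The article declares three primaries without order and scores two. It states one sample size at unadjusted two-tailed P<.05 and gives no rule linking them. Followed as written on the two scored outcomes, the plan carries a familywise error of about 7–10% instead of 5%; a leadership test would make it 8–14%. The range reflects an assumed correlation.

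Controlling the error rate costs modest power rather than invalidating the sample size. At 77 per group, per-outcome power under Holm falls from 80% to about 76–78% if both effects are real at correlations up to 0.7, and to about 71% if only one is. These figures rest on the back-solved d=0.454 and on independent students; a clustering allowance would lower them. At about 90 per arm most of the loss disappears. This should be corrected before analysis, but it does not undermine the trial.

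**What to change.** 1. In Outcomes, name the two PSRQ subscale scores, personal and social responsibility, as the primary outcomes. State that each is compared between arms, with Holm's procedure at overall two-sided .05.
2. Label leadership, PACES-PE and the repeated measures multivariate ANOVA as secondary or exploratory, and make the abstract, Outcomes, Measurement Tools and Intervention Design sections agree.
3. In Participants, state the power together with the rule. For example: with 77 per group and an assumed d of 0.454, power per outcome is about 71% at the first Holm step and about 76–78% under full Holm if both effects are real (correlation up to 0.7); 80% at the first step requires d of about 0.50; all before any clustering allowance.

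A pre-stated fixed sequence of the two scores is an acceptable alternative. It keeps 80% for the first outcome, at the price of testing the second only if the first succeeds.

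The cost is a slightly less favourable stated power and a dated amendment to the registered outcomes. The Results section says data collection has begun and schedules analysis for October 2025, so the amendment has to be dated before that analysis. No extra students are needed.

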### Participants

The participants in this study will be students from years 5, 6, and 8. Each intervention group in the study will need to have 77 students and a matched control group of the same size to detect 2-tailed statistical significance (*P*<.05) with 80% power (1−β=0.8). Two schools in the western suburbs of Sydney have been recruited to participate in the study: one is a government high school, and the other is an independent K-12 school. They have been chosen through professional networks who expressed interest in the TPSR study. Students in NSW generally participate in 1 PE lesson per week, which is where the intervention will take place. PE lessons in NSW high schools are delivered to students from years 7 to 10 and focus on skills development, alongside one or two sport lessons focused on game play.

Consent will be obtained from parents, students, and the school principals in line with the ethics requirements of the University of Sydney. Participants’ personal information and school names will be deidentified in all publications arising from the study. Students and teachers will also be briefed on the intervention before study commencement and given the opportunity to ask questions. Participants will be allowed to withdraw from the intervention at any time. All data collected, including data from focus interviews, surveys, meeting minutes, and consent forms, will be stored securely and encrypted with a password. If parents request details of intervention results, a lay summary will be provided.

Fidelity and acceptability will be addressed through teacher expertise and training, intervention location, timetabling, and time spent on the intervention. Teachers will participate in a professional development program before starting the intervention. The purpose of this program is to familiarize teachers with the TPSR framework and to facilitate the co-design of strategies and activities to integrate the framework into programs. This approach also means that students do not have to build relationships with or adapt to outside facilitators. Furthermore, it does not incur additional funding for the school or research team. The professional development program will comprise a 3-hour, face-to-face learning block before the intervention and ongoing check-ins with teachers using Zoom (Zoom Video Communications, Inc) for the duration of the intervention.

The intention of the co-design process is to limit disruption to teachers and their practice as well as to create a mutually agreed-upon implementation of the TPSR framework in existing units. The co-design process allows both parties to benefit from sharing information that aims to improve currently established protocols and promotes sustainable practice within the school and with teachers [28]. Co-design principles can be applied at any stage of an intervention but may target three main components: (1) defining the problem, (2) designing a solution, and (3) implementation [29]. Throughout this intervention, teachers will work with researchers to identify social issues at their school; they will then work with researchers to apply TPSR principles to address these issues; and, finally, they will be involved in facilitating PE lessons that implement these principles with students. The co-design process aims to “share power” between the 2 parties taking part in the research with the mutual aim of improving outcomes [29]. This process will enable the research team and teachers to navigate the intervention in a collaborative manner, strengthening the planning process before intervention commencement.

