**Methods:**

This study will use a nonrandomized controlled trial design with a qualitative evaluation to assess feasibility and acceptability. Data will be collected through student surveys, student focus groups, and teacher reflection journals. Two schools in New South Wales, Australia, will participate by implementing the TPSR framework in their programs. Schools will include classes in stages 3 and 4 of the intervention, involving approximately 90 students from each school. Both schools are located in Sydney, New South Wales: one is a government high school, and the other is an independent K-12 school. To address feasibility and accessibility concerns, the intervention will be delivered during regularly scheduled PE classes. It will be facilitated by students’ regular PE teachers, who will also participate in ongoing professional development and be involved in a co-design process with the research team. Primary outcomes include reporting on personal responsibility, social responsibility, and leadership behaviors, measured using two tools: (1) the Tool for Assessing Responsibility-Based Education and (2) the Personal and Social Responsibility Questionnaire. A secondary outcome, enjoyment, will be assessed using the Physical Activity Enjoyment Scale–Physical Education version. Feasibility and accessibility will also be examined as secondary outcomes.

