### Study Design

The protocol was developed according to the SPIRIT (Standard Protocol Items: Recommended for Interventional Trials) statement (Multimedia Appendix 1).

The study will use a nonrandomized controlled trial design with a qualitative evaluation to assess feasibility and acceptability. This method has been chosen for several reasons. First, one of the criticisms against the TPSR model is that it favors qualitative studies and has been underresearched using quantitative methodologies [11]. To address this, we will use both qualitative and quantitative methods in this study. The concern regarding the limited use of quantitative approaches was echoed in a systematic review on TPSR interventions that found that only 4 of the 22 included studies used exclusively quantitative methods, questioning the validity of the framework outside of qualitative research [26]. Studies have consistently called for greater use of quantitative analysis of the TPSR framework in research [10,11,26]. Furthermore, to obtain the most accurate representation of the effect of the framework in Australian schools, teachers, and students, this approach is deemed most suitable because it uses both qualitative and quantitative analysis and is able to factor in a complex landscape such as education [27]. In this study, data will be collected through student surveys, focus groups, teacher reflection journals, and the Tool for Assessing Responsibility-Based Education (TARE).

We will recruit at least 6 classes from each school participating in the intervention, which will amount to approximately 3 classes in the control group and 3 in the experimental group (Figure 1).

Upon recruitment of the schools and selection of individual classes by each principal, researchers will collaborate with intervention facilitators to implement the TPSR framework during the intervention “season.” Table 1 presents example strategies that can be implemented in a TPSR study and will be shared with teachers during the co-design process.

A timeline of the intervention is presented in Table 2.

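### The 80% power attached to 77 students per group shows no allowance for allocation by class, and it is unclear whether the figure applies per school or to both schools pooled

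*Protocol article*

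**What the plan says.** The sample-size statement is in Methods, Participants: "Each intervention group in the study will need to have 77 students and a matched control group of the same size". It ties this number to two-tailed testing at P<.05 and 80% power. It names no outcome, effect size, standard deviation, class correlation or attrition rate.

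Study Design describes how students enter the arms. It refers to "selection of individual classes by each principal" and to at least 6 classes from each school, "which will amount to approximately 3 classes in the control group and 3 in the experimental group". With two schools that is about 6 classes per arm, as a minimum.

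The abstract's Methods paragraph gives the expected enrolment: "involving approximately 90 students from each school".

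Quantitative Analysis plans an ANOVA of questionnaire scores before and after the intervention, and a repeated measures multivariate ANOVA.

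**The concern.** Students in one PE class share a teacher, a timetable and each other, so their responsibility scores are likely to be correlated. When whole classes are allocated, the information depends on the number of classes as well as the number of students. A power figure that counts only students will then be too high. Here the required number is given in students, and nothing links it to the class structure set out in Study Design.

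The scope of the number is also unclear. "a matched control group of the same size" for each intervention group could describe one comparison per school or one comparison over both schools, and the abstract's enrolment figure meets the requirement on some readings but not on others.

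The study is justified partly by a call for stronger quantitative evidence on this teaching model. Readers will use the stated power to judge how much a quantitative result can carry.

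**Working it through.** **Inputs from the article.** 77 per group, 1:1, two-sided 5%, 80% power (Participants). About 3 classes per arm per school, so k = 6 per arm (Study Design). About 90 students per school, so about 180 in all, 90 per arm and 90/6 = 15 per class if the arms are pooled (abstract).

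**Assumptions, not in the article.** ICC 0.02, 0.05 and 0.10. Correlation between baseline and post-test r = 0.6, reducing variance by the same share between and within classes. Degrees of freedom 12 classes − 2 arms − 1 for school = 9. No dropout.

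**Step 1: what 77 corresponds to.** Without an effect size, 77 cannot be reproduced forwards, so it is solved backwards. Normal approximation: d = (1.960 + 0.842) × √(2/77) = 0.452. Two-sample t-test: d = 0.454. A rounded d = 0.45 gives 2 × 2.802²/0.45² = 77.5, that is 78. The number therefore fits an unclustered comparison at about 0.45. Another origin is possible: d = 0.50 needs 63 per group, and 63 inflated by about 1.22 is also 77.

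**Step 2: power for the class design.** With n students per arm and m = n/6 per class:

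- design effect DE = 1 + (m − 1) × ICC
- noncentrality λ = 0.454 × √[n / (2 × DE × (1 − r²))], with r = 0 when unadjusted
- power from the noncentral t on 9 df (critical value 2.262)

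Example: n = 90, ICC 0.05, unadjusted. DE = 1 + 14 × 0.05 = 1.70; λ = 0.454 × √(90/3.40) = 2.34; power 55%.

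| Students per arm | Analysis | ICC 0.02 | ICC 0.05 | ICC 0.10 |
|---|---|---|---|---|
| 77 (m = 12.8) | unadjusted | 62% | 51% | 40% |
| 90 (m = 15) | unadjusted | 67% | 55% | 42% |
| 90 (m = 15) | baseline-adjusted | 85% | 74% | 59% |
| 180 (m = 30) | unadjusted | 86% | 69% | 50% |
| 180 (m = 30) | baseline-adjusted | 97% | 86% | 68% |

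The 180 rows apply if the abstract's 90 means intervention students per school, with as many controls.

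**Step 3: detectable difference.** 80% power on 9 df needs λ of about 3.15, so the detectable difference is 3.15 × √[2 × DE × (1 − r²)/n]. At 90 per arm it is 0.53, 0.61 and 0.73 SD unadjusted. Multiplying by √(1 − 0.36) = 0.8 gives 0.42, 0.49 and 0.58 SD adjusted.

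**Step 4: scope of 77 + 77.**

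- Per school, with 90 as all students in a school: 154 needed against about 90. The 45 per arm would give λ = 0.454 × √(45/2) = 2.16 and about 57% power even without clustering.
- Pooled over schools: 154 needed against about 180. Met.
- Per school, with 90 as intervention students only: 77 needed against about 90. Met.

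**The case against.** The strongest reply is that no arithmetic in the article is shown to be wrong. That stands: the origin of 77 is inferred, and every power figure above is conditional on the implied 0.454. A reader might infer that 77 is proven to be an individual-level calculation. The article gives no formula, so that goes too far, although nothing in the text points to an inflation factor either.

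A reader might also infer that power is well below 80% in every case. The documents do not support that. The questionnaire is given before and after the intervention and a repeated measures analysis is planned, so an unadjusted post-test comparison is not the natural benchmark. With adjustment, 90 per arm reaches 85% at ICC 0.02, and 180 per arm reaches 86% at ICC 0.05. Six classes per arm is a minimum, and more classes would help.

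The per-school shortfall is tempting to call a contradiction, but two of the three readings in Step 4 meet the target. It is an ambiguity.

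The absent effect size is not a fault by itself, since a journal article may leave it to a fuller document. Nor does anything in the article say that a null result would be read as showing no effect; Objectives frames the design around feasibility and acceptability.

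One reply does not help: that a student-level ANOVA would keep the power. Treating students as independent at 15 per class and ICC 0.05 turns a nominal 5% error into 2 × [1 − Φ(1.96/√1.70)], about 13%.

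**Conclusion.** The point holds in a limited form. The article states a required number and a power, and separately states allocation by class, and nothing in it connects the two. At the implied difference of about 0.45, the 80% figure is secured only if the ICC is low or baseline adjustment is effective. Over the readings and assumptions in the table, power runs from 40% to 97%. Even the most favourable reading, 180 per arm with adjustment, falls to 68% at ICC 0.10.

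The conclusion rests on the inferred effect size, the assumed ICC range, r = 0.6, 9 df and 6 classes per arm, none of which except the number of classes comes from the article. The scope of 77 plus 77 needs clarifying whatever the ICC. This should be fixed, but it does not invalidate the study. Confidence is moderate.

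**What to change.** Keep the enrolment. The Results section says that recruitment concluded in December 2024, so the remedy lies in the wording and the reporting:

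1. State that the two arms are pooled over both schools, if that is the intention, and whether the abstract's 90 counts all students in a school or only intervention students.
2. Give the effect size and the outcome behind 77.
3. Replace the unqualified 80% with the power or detectable difference for the actual number of classes, over an ICC range such as 0.02 to 0.10, with baseline adjustment and its assumed correlation stated.
4. Report the Personal and Social Responsibility Questionnaire effect with a confidence interval that accounts for class.

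The cost is one rewritten paragraph and an analysis that accounts for class. No extra students are needed. The drawback is that the stated power will look less favourable.
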